### Intervention

The ‘PERANTARA’ is a self-help psycho-education material package that consists of both printed and audiovisual material (see Table 1). The word PERANTARA is Indonesian for ‘mediator’ or ‘facilitator’. PERANTARA is abbreviation for “Pengantar PERAwataN kesehaTan payudARA”, which means ‘introduction to breast health treatment’. The conceptual framework (blueprint) of PERANTARA was developed based on semi-structured interviews with 27 breast cancer patients and 5 focused group discussion sessions with healthcare providers (5 oncologists and 15 nurses). The conceptual framework (blueprint) was then reviewed by a panel consisting of a health psychology expert, a healthcare communication expert, an oncologist, and a breast cancer survivor. The researchers obtained suggestions and comments on the intervention blueprint and also the usability and acceptability of the developed interventions. The panel also recommended to have the printed and audiovisual material be developed by a team of audiovisual professionals. The PERANTARA provides the following information: 1) a brief explanation of breast cancer in order for the patients to have an accurate understanding and stimulation to seek information from reliable sources (oncologist); 2) an explanation of the breast examination procedure to raise the patients’ awareness on their symptoms and willingness to follow this procedure; 3) recommendation to seek support from significant persons and institutions. The audiovisual material is an 8 min and 33 s length video featuring two breast cancer survivors who shared their stories about their conditions, promoting active coping and seeking social support.

**Table 1 Tab1:**
[figure not shown]
Overview of PERANTARA Package

The prototype of PERANTARA was piloted within 13 patients and with oncologists and survivors. Results from this pilot study showed that the prototype was feasible and acceptable to use. Trained research assistants will give the PERANTARA to the experimental groups. They will give a brief explanation to the patient regarding PERANTARA and instructions on how to use it.

### Treatment as usual (TAU)

TAU in a district hospital usually consists of consultation with the oncologist about the medical examination procedures. Information related to breast health is limited, and usually entails nothing more than a poster on the wall in the hospital waiting room. Psychosocial services for patients with breast complaints to support the patient during the examination process are not provided at all four hospitals participated in the study. The research assistants will keep track of all services received by the patients during the course of the study.

### Instruments

#### Primary outcome

Diagnosis delay will be the primary outcome measure. This is defined as the time between the date of the first consultation at the hospital and the date of the definite breast cancer diagnosis based on pathological examination. This outcome will be measured using the Diagnostic Delay Interviewer Guide. This instrument has been developed by the researchers and consists of the following questions: (a) What was the date that you consulted with a doctor in the hospital?, (b) What was the date that you received the breast cancer diagnosis?, and if there was a consult delay (c) What were the reasons for delay? A distinction will be made between delay due to the patient and due to the doctor. This tool will be pilot-tested before the final data collection is done.

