## Abstract

**Background:**

Breast cancer (BC) is the most frequent cancer occurring in women across the world. Its mortality rate in low-middle income countries (LMICs) is higher than in high-income countries (HICs), and in Indonesia BC is the leading cause of cancer deaths among women. Delay in breast cancer diagnosis negatively impacts cancer prognosis. Only about 30% of patients who come to the hospital to check on their breast abnormalities, continue thorough examination to biopsy to get a diagnosis based on the results of anatomical pathology. Many Indonesian women with breast cancer were already in an advanced stage when starting treatment. Therefore, delay in diagnosis is a serious problem that needs to be addressed. The present study will investigate whether our newly developed self-help psycho-educational programme, “PERANTARA”, for women with breast cancer symptoms is effective to reduce patient diagnosis delay in Indonesia.

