## Background

Breast cancer (BC) is the most frequent cancer occurring and the leading cause of cancer-related deaths in women, with an estimated 1.67 million new cancer cases diagnosed and 522,000 deaths in 2012 [1]. The incidence of breast cancer in LMICs is lower as compared to HICs (25.8 vs 95 per 100.000), but a major concern in LMICs is the higher mortality despite its lower incidence (12.7 vs 17.1 per 100.000) [2]. In Indonesia, BC is the most prevalent cancer among women with an incidence rate of 48,9 and a mortality rate of 19,8 women per 100,000 [3].

One of the reasons for the high mortality of breast cancer in LMICs is the fact that most cancer in LMICs is detected at later stages. Review on delay of diagnosis revealed that more than 70% of breast cancer patients in most HICs are diagnosed in Stages I and II, compared with only 20 to 50% of patients in the majority of LMICs [4]. In Indonesia, about 60%–70% of patients had their first BC-related visit to the hospital when the disease was already in advanced stages (III and IV) [5–7].

Diagnosis delay, the time between seeking medical advice and the date of final diagnosis based on pathological examination (i.e. biopsy), remains a serious problem. Studies have shown that diagnosis delay of over 3 months is associated with a bigger tumour size, positive lymph nodes, high incidence of late clinical stages, and metastatic disease [8, 9]. Delay in diagnosis predicts worse clinical outcomes [10]. The delay may cause mortality of the patient. A previous qualitative study involving 50 BC patients in Indonesia found that 35 participants (70%) were delayed in seeking help, with the time of delay ranging from 4 to 24 months, except for the four participants who had delayed for 4 years, 10 years, 3 years, and 15 years, respectively [11].

Previous studies found that delay in diagnosis among women with breast cancer symptoms was a result of a complex interaction of several factors, which often concern characteristics of the patients and the health care system. Several studies state that patients-related factors are a major concern and need to be addressed in an intervention program (e.g. lack of knowledge and awareness about breast cancer). For example, a study in Moroccan women found that diagnosis delay is also a very important health problem in Moroccan women, particulary caused by a lack of knowledge, information and awareness regarding breast cancer [12].

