## Methods

### Design

The study will be a multicentre, cluster-randomized controlled trial (cRCT), with hospitals as the unit of randomisation (clusters). We will include four hospitals in Bandung, Indonesia that have agreed to participate in this study. Because of the limited number of hospitals, we will use a cross-over design in which in each hospital will be given PERANTARA or control (treatment as usual (TAU)) at successive periods. Because every hospital forms its own control, the cross-over design can produce results with a smaller sample size than required with a parallel design. The order in which the hospital receives PERANTARA is randomly determined. The study will compare the PERANTARA to TAU in women with suspected breast cancer. This study uses two predefined periods. In the first period, two hospitals will have the experimental group (the patient is given the intervention and TAU) and two other hospitals will have the control group (patients only receive TAU). In the second period, it is the other way around.

The primary outcome is diagnosis delay in terms of the time between the date of the first consultation at the hospital and the date of final breast cancer diagnosis based on pathological examination. Secondary outcomes are breast cancer knowledge, anxiety and depression, and quality of life, as well as treatment delay.

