### Participants

This study will include 106 patients in the cRCT, 53 participants in the Treatment-as-Usual (TAU) control group and 53 participants in the experiment/intervention group. Power calculations suggest a minimum sample size of 41 participants per group (power = 0.80, alpha = .05 two-sided). Taking into account 30% attrition at follow-up, at least 106 participants (53 per group) need to be included. Participants will be recruited from four district hospitals in Bandung, West Java, Indonesia, that are representative for the health care facilities in the different areas in Bandung, Indonesia.

Participants will be new patients (outpatients) who visit the hospital with breast symptoms, which make them suspects of having breast cancer. Patients eligible for the intervention program will be asked to take part in the study when reporting at the district hospitals. The following inclusion criteria will be used: women with age > 18 years, an adequate command of the Indonesian language and no major psychiatric disorder. The last is determined by checking the medical record on a consultation history/record with the Psychiatric Department. Patients who have been seen by psychiatrists are excluded from the study.

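### The primary outcome ends at a confirmed breast cancer diagnosis although women are enrolled on symptoms, so benign and never-biopsied women have no outcome value, and the Background defines the same delay differently

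*Protocol article*

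**What the plan says.** The protocol article gives the end of the delay interval in four places.

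- Background: "the time between seeking medical advice and the date of final diagnosis based on pathological examination (i.e. biopsy"). This is not limited to cancer.
- Design: "the date of final breast cancer diagnosis based on pathological examination".
- Primary outcome: "the date of the definite breast cancer diagnosis based on pathological examination".
- Interviewer guide, question (b): "What was the date that you received the breast cancer diagnosis".

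The enrolled population, under Participants, is "new patients (outpatients) who visit the hospital with breast symptoms, which make them suspects of having breast cancer". No criterion requires a biopsy or a confirmed cancer. The section on secondary outcomes puts the treatment-delay question only to women with a positive diagnosis, so the authors expect some women without one.

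The Abstract reports that "Only about 30% of patients who come to the hospital to check on their breast abnormalities, continue thorough examination to biopsy". The Intervention section says that the material on the examination procedure is meant to raise "willingness to follow this procedure".

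The Analysis plan names a three-level HLM of delay scores over time and mentions no censoring. The sample size is 41 per group, raised to 53 per group for 30% attrition at follow-up.

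**The concern.** A woman who goes promptly to biopsy and has a benign result has done what PERANTARA asks, yet she never reaches the endpoint. A woman who is never biopsied does not reach it either. An HLM of a continuous delay score can use only women with an end date, and the article gives no rule for the others.

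The two groups matter for different reasons. Malignancy is a baseline state that a leaflet and a video cannot change, so losing benign women mainly shrinks the sample. Women not biopsied are the source of bias. A cancer becomes known only if she is biopsied before follow-up ends, and biopsy uptake is what the intervention targets. If PERANTARA brings hesitant women to a late biopsy, their long delays enter the intervention mean, while similar control women contribute nothing. An effective programme could then look ineffective or harmful on its own primary outcome.

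**Working it through.** **1. The plan's own figure.** 41 × 1.30 = 53.3, taken as 53 per group, and 2 × 53 = 106. This reproduces the stated total. (Dividing by 0.70 would give 59 per group, which is a separate matter.) The article states no effect size. Solving the two-sample t-test for n = 41 per group, two-sided alpha 0.05 and power 0.80 gives d = 0.626. The normal approximation, (1.960 + 0.842) × √(2/41), gives 0.619.

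**2. Women with an outcome value.** n per arm = 53 × biopsy share × malignant share. The biopsy share is the Abstract's 30%, assumed here to apply to both arms. The malignant share is not in the article, so a range is assumed. Power is from the t-test at d = 0.626 and ignores clustering and cross-over, because no intracluster correlation is given.

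| Women counted | n per arm | Power |
|---|---|---|
| Planned evaluable | 41 | 80% |
| 30% attrition only (53 × 0.70) | 37 | 76% |
| Any pathology date (53 × 0.30) | 15.9, about 16 | 40% |
| 75% malignant | 11.9, about 12 | 31% |
| 50% malignant | 8.0, about 8 | 21% |
| 25% malignant | 4.0, about 4 | 12% |

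The attrition allowance alone accounts for little of the loss.

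**3. Direction of the bias.** Follow-up is 12 weeks after a post-assessment that falls 1 to 2 weeks after enrolment, or about 13 to 14 weeks in all. Take 97 days. All other figures in this step are assumed.

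*PERANTARA adds late biopsies.* In the control arm 30% are diagnosed, with mean delay 26 days. The intervention arm has the same women plus an extra share diagnosed evenly over days 30 to 97 (mean 63.5). The mean among diagnosed women is (0.30 × 26 + a × 63.5) / (0.30 + a):
- a = 0.10: 14.15 / 0.40 = 35.4 days
- a = 0.20: 20.50 / 0.50 = 41.0 days
- a = 0.30: 26.85 / 0.60 = 44.8 days

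More women are diagnosed, yet the observed delay is longer.

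*PERANTARA speeds up everyone equally.* With exponential times and a proportion p diagnosed by day 97, the mean among those diagnosed is 97 / (−ln(1 − p)) − 97(1 − p)/p:
- p = 0.30: 272.0 − 226.3 = 45.6 days (from unrounded terms)
- p = 0.50: 139.9 − 97.0 = 42.9 days

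A rise from 30% to 50% diagnosed appears as a difference of under 3 days.

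**4. The alternative outcome.** Use time to any definitive pathology result, with women without one censored, so that all 106 contribute. Take 30% with a result in the control arm and an assumed p in the intervention arm. Then HR = ln(1 − p)/ln(0.70), events = 53 × (0.30 + p), and power = Φ(√events × ln(HR)/2 − 1.96), again ignoring clustering.

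| p | HR | Events | Power, 53 per arm | Power after 30% loss |
|---|---|---|---|---|
| 0.40 | 1.43 | 37.1 | 19% | 15% |
| 0.50 | 1.94 | 42.4 | 58% | 44% |
| 0.60 | 2.57 | 47.7 | 90% | 78% |

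The new outcome repairs the comparison, but 80% power at 106 is reached only for a large rise in uptake.

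**The case against.** **Loose drafting.** The Background definition is close to the outcome proposed here, so the cancer-specific wording may be a slip. That is a fair reason to call this a conflict to be reconciled. It does not remove the defect, because the formal definition appears twice in cancer-specific form and the instrument asks for that date alone.

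**Left to the analysis plan.** Rules for women without an end date are often set there. That would hold if the article were silent. It fixes the endpoint, the question and the model, and together they leave these women without a value.

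**Analysis set not stated.** A reader might infer that the trial has decided to analyse confirmed cancers only, or to score benign women as maximal delay. No section says either. The selected comparison is what follows from applying the plan as written.

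**Benign women and bias.** A reader might infer that leaving out benign women in itself breaks the randomised comparison. It does not, for the reason given above.

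**Power figures.** The value of d is back-solved. The 30% describes women attending with breast abnormalities, and the share among enrolled suspects may differ. Applying 30% to both arms assumes no effect on uptake, whereas the bias argument assumes one. With 16 against 32 biopsied (uptake doubled, assumed), power at the same d is 52%. All of this stands, so the figures illustrate scale and are not estimates of the trial's power.

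**Conclusion.** The point holds as a wrongly fixed and inconsistently defined endpoint. The primary outcome has no value for benign or never-biopsied women, and the named model cannot include them. This rests on the text alone and is firm. The bias is confined to women whose cancer is found or missed according to biopsy within follow-up. Its size is unknown, and it can run against the intervention.

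The loss of power is illustrative: about 40% with any pathology date, and 31% to 12% over an assumed malignant share of 75% to 25%, against a planned 80%. These figures depend on a back-solved d of about 0.63, the background 30% in both arms, and no allowance for clustering or cross-over. The endpoint should be settled before data collection.

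**What to change.** - Reconcile the Design and Primary outcome sections with the Background. Define the primary outcome for all enrolled women as time from first hospital consultation to the definitive pathology result, benign or malignant. Censor women without a result at the 3-month follow-up.
- Reword question (b) to ask for the date of the pathology result, and take that date from the medical records. The tool is still to be pilot-tested and records are already reviewed, so no new procedure is needed. The 3-month review, now described for treatment delay, must be extended to pathology dates for every woman.
- Replace the HLM for this outcome with a time-to-event analysis that accounts for hospital and period. The HLM can stay for the questionnaire scores.
- Keep time to cancer diagnosis among confirmed cancers as a supportive analysis, labelled as a selected subset.
- Restate the power for the new outcome at the planned 106, with the effect size and the control-arm share given.

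Cost: the primary analysis and the power statement must be rewritten, and not just the endpoint wording. The outcome would measure completion of work-up rather than cancer-specific delay. Women whose work-up properly ends without a biopsy would still be censored as having no result, so that part of the problem remains and should be acknowledged.

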**Fig. 1 Fig1:**
[figure not shown]
Flowchart of The Procedure

Participants in the control group will receive treatment as usual (TAU), while the intervention group will receive the PERANTARA package (which consists of printed and audiovisual materials). Participants will be requested to read and watch the intervention package within 7 days.

The post-intervention assessment will take place 7 days after the intervention. Participants will be asked to fill in the following questionnaires: (1) the Diagnostic Delay Questionnaire; Quality of Life (2) WHOQOL-Bref and (3) EQ-5D 5L; (4) HADS; (5) BCKT; (6) Intervention Material Feedback Form.

The follow up assessment will be scheduled at 3 months (12 weeks) after the post-intervention assessment. The Participant will be requested to fill in: (1) The Diagnostic Delay Questionnaire; Quality of Life (2) WHOQOL-Bref and (3) EQ-5D 5L; (4) HADS; (5) BCKT. The researcher will review the medical record of the patient to registrate the occurence of treatment delay. This period is chosen because it is also a criterion for treatment delay.

Trained research assistants with a background of psychology will conduct the assessments. All research assistants have received a 5-days workshop covering how to administer the instruments, information on common psychosocial needs of breast cancer patients, general interview techniques, and how to take a neutral role instead of a therapeutic role. Ongoing monitoring will be conducted through regular supervision by the main researcher (HS) supervised by the principle investigators.

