#### Secondary outcome

A standard socio-demographic and medical history form (SDMH) will be used to collect patients’ background data on ethnicity, age, marital status, religion, education level, employment status, income level, travel time to hospital, insurance status, mental health status, family history of cancer and use of traditional healer. The patients’ medical records will also be reviewed to obtain data on type and stage of cancer and type of treatment.

Patient knowledge will be assessed using the Breast Cancer Knowledge Test (BCKT). The BCKT is a 20-item questionnaire that was developed and tested to determine (a) general knowledge of breast cancer; and (b) the relationship between the knowledge of breast cancer and utilization of screening practices. The BCKT consists of 2 subscales; one subscale of 12 items to measure general knowledge and one subscale consisting of 8 items to measure knowledge of curability. In the first section, item number 3 about the breast cancer prevalence was adjusted with the actual Indonesian prevalence rate. The total score ranged from 0 to 20, with higher scores indicating higher breast cancer knowledge. The BCKT has an acceptable reliability coefficient (α = 0.69). The Breast Cancer Knowledge Test (BCKT) has been translated into Indonesian using the forward-backward translation method [24].

Symptoms of anxiety and depression will be measured with the Hospital Anxiety and Depression Scale (HADS). The HADS is a 14-item self-report questionnaire that was developed to assess psychological distress in people with medical illness. It consists of 2 subscales: 7 items to measure anxiety (HADS-A) and 7 items to measure depressive symptoms (HADS-D). Psychometric properties of the Indonesian version of the HADS were adequate, with values of Cronbach’s coefficient (alpha) being 0.77 and 0.74, respectively [13].

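### Both dates of the primary outcome come from the patient's own report in an open assessment, with no stated check against the records that the trial already reviews for other items

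*Protocol article*

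**What the plan says.** In the protocol article, under Instruments, Primary outcome, diagnosis delay is "the time between the date of the first consultation at the hospital and the date of the definite breast cancer diagnosis based on pathological examination". The Design section gives the same two endpoints. On measurement, the Primary outcome section says: "This outcome will be measured using the Diagnostic Delay Interviewer Guide". The researchers wrote this guide themselves, and "This tool will be pilot-tested before the final data collection is done". Its two date questions are put to the patient: "What was the date that you consulted with a doctor in the hospital" and "What was the date that you received the breast cancer diagnosis". A third question covers reasons for delay.

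The Procedure section schedules the delay instrument at the post-intervention assessment and again at follow-up, 12 weeks later. It also says of the follow-up stage: "The researcher will review the medical record of the patient to registrate the occurence of treatment delay". Under Secondary outcome: "The patients’ medical records will also be reviewed to obtain data on type and stage of cancer and type of treatment". The same section has treatment delay asked of the patient and then verified in the hospital records.

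On staffing, the Intervention section says: "Trained research assistants will give the PERANTARA to the experimental groups". The Procedure section has trained research assistants conduct the assessments. The Design section allocates whole hospitals to one condition per period.

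**The concern.** The outcome is defined by two events that a hospital would ordinarily document, yet it is measured by what the woman says. Three things follow.

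- **Mismatch with the definition.** The definition ends at the pathological diagnosis, whereas the question asks when the woman received it. If she returns late for her result, the second date is later than the first. PERANTARA aims to raise willingness to go through the examination procedure, so this gap could differ between conditions.
- **Recall and reporting error.** A reported date may be wrong, and women who know they were given material about prompt examination may report differently from those who were not.
- **Dependence on attendance.** The article plans for 30% attrition at follow-up. A woman who is diagnosed after the post-intervention assessment and misses the 3-month interview has no reported diagnosis date, even if her hospital holds one.

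What is at stake is the validity of the endpoint on which the trial's main conclusion rests.

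**Working it through.** No figure in the article needs to be reproduced here. The check sets the stated data sources side by side.

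| Item | Status in Methods | Stated source | Record used? |
|---|---|---|---|
| Date of first hospital consultation | Primary outcome, start | Question to the patient | None stated |
| Date of pathological diagnosis | Primary outcome, end | Question to the patient | None stated |
| Treatment delay | Secondary outcome | Question to the patient | Yes, at follow-up |
| Cancer type, stage and treatment | Background data | Medical record | Yes |

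(The Abstract names treatment delay alongside diagnosis delay as primary. The table follows the Design section.)

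1. **Is the source fixed, or merely left out?** It is fixed. The Primary outcome section names the instrument and lists its questions. The same instrument appears in the Procedure and Analysis plan sections as a questionnaire. The mode is therefore unsettled, but the source is patient report either way.

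2. **Do the questions match the definition?** The end-date question does not: being told and being diagnosed are different events. The start-date question does not specify the first consultation. That matters little, because participants are new outpatients enrolled when they report to the hospital.

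3. **Is the assessment open?** The article does not use that word, and it describes no blinding. Women know whether they were handed a package. Condition follows from hospital and period. One staff role both gives and explains the package and conducts the assessments, and the post-intervention assessment includes a feedback form on the material. Taken together, the assessment is open in effect.

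4. **Could the record supply the dates?** This is an inference, but a reasonable one. The outcome is a pathological diagnosis, and cancer type and stage are to be taken from the same records. The article does not say that pathology dates are complete or held on site.

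On the stated sources, a secondary outcome is verified against records and the primary outcome is not.

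**The case against.** Several points count against making much of this.

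- **Recall of the start date is easy.** Enrolment takes place when the woman reports to the hospital, so the first consultation falls at or near a study contact. This stands. The recall concern applies mainly to the diagnosis date, over roughly three months.
- **Calendar dates leave little room for assessor judgement**, and the assistants are trained to stay neutral. This stands in part. The article does not say that the same assistant delivers the package to a woman and then assesses her. Neutral conduct does not, however, remove the woman's own knowledge of her condition.
- **The article is condensed.** Source verification may be set out in the full protocol, and the section on usual treatment has assistants track services received. But the article names a source for this outcome and a record check for another, so this is a stated choice. Tracking services is not described as a source for the two dates.

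A reader might infer a sizeable power gain. Thirty per cent of 106 is about 32 women, leaving 53 × 0.70 ≈ 37 per group. The article gives no effect size, but 41 per group at 80% power (two-sided 0.05, t-test) back-solves to d ≈ 0.626. At that d, power would be about 0.76 with 37 per group and 0.89 with 53, ignoring clustering. The documents do not support this reading:

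- The calculation needs a completed interval for every woman. Someone who stops attending before biopsy has no pathology date at that hospital to recover, and the Abstract says only about 30% of patients who come with breast abnormalities go on to biopsy.
- Women diagnosed by the post-intervention assessment have already been asked for the date there, so missing the 3-month visit does not always lose the outcome.

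**Conclusion.** The point holds as one about data source. The primary outcome is defined by a pathological diagnosis but measured by patient report in an effectively open assessment, one of its two questions asks about a different event, and the record review already planned is not used for it. This is stated in the article, apart from two inferences: that assessment is open in effect, and that the record usually holds the pathology date.

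It applies to the main endpoint for every enrolled woman, but its numerical effect cannot be derived. The article gives no recall error, no gap between pathological diagnosis and disclosure, and no rate of record completeness, so no power gain can be quantified. Record use would yield less recall error and reporting bias, a measure that matches the definition, and known diagnosis status for some women who miss the 3-month interview. It would not settle how women without a diagnosis are to be analysed, which is a separate question. The change is worth making because it is cheap; the point does not by itself invalidate the design.

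**What to change.** In the Primary outcome section, state that:

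1. Both dates, first hospital consultation and pathological diagnosis, are taken from the hospital and pathology record for every enrolled woman, within the record review already planned, whether or not she attends follow-up.
2. Where no pathology report exists, the review records that no diagnosis had been made at that hospital by the review date, and gives that date.
3. The interview is kept for the reasons for delay, and as a back-up for a date when no record exists, for example after diagnosis elsewhere. The source of each date is noted.

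Concealing the condition from the person abstracting the dates is optional. With allocation by hospital and period, a calendar date at a known hospital may reveal the condition to anyone who knows the order, so concealment would be hard to achieve.

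The cost is a change of wording, two more items to abstract per woman, and some incomplete records for which the interview must stand in.

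### The primary outcome ends at a pathology-based diagnosis, but the interview question asks when the patient received the diagnosis and no record check is stated, so the defined interval is not secured

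*Protocol article*

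**What the plan says.** The Primary outcome section of the protocol article gives this definition of diagnosis delay: "the time between the date of the first consultation at the hospital and the date of the definite breast cancer diagnosis based on pathological examination". The Design section gives the same end point: "the date of final breast cancer diagnosis based on pathological examination".

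On measurement, the Primary outcome section says: "This outcome will be measured using the Diagnostic Delay Interviewer Guide". It then lists the guide's questions. The start date comes from "a) What was the date that you consulted with a doctor in the hospital" and the end date from "b) What was the date that you received the breast cancer diagnosis". A further question asks for reasons for delay. The tool is still to be pilot-tested.

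Medical records are used for other items. The Procedure section says of the 3-month follow-up: "The researcher will review the medical record of the patient to registrate the occurence of treatment delay". The Secondary outcome section adds that the patient's answer on starting treatment is checked against hospital records, and that records supply cancer type, stage and treatment. No section says that the two dates forming the primary outcome are taken from records or checked in them.

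**The concern.** The end date in the definition is tied to pathology; the end date in the question is tied to what the patient was told. The question leaves two other dates open:

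- the day she learned the result, which may fall after the pathology result if she has to return for it;
- the day a doctor gave a clinical diagnosis, which may fall before any pathology.

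The first lengthens the measured delay relative to the definition and the second shortens it. A woman who never has a biopsy has no end date under the definition, yet she could still answer the question.

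What is at stake is whether the trial's estimate refers to its own primary outcome. The time until a woman returns for her result is partly her own behaviour, and the intervention is meant to change behaviour, so the gap need not be equal in the two arms. Research assistants both hand out the package and conduct the assessments, and no blinding is described. That makes a date from an independent source more valuable.

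**Working it through.** The plan gives no figure for the gap between pathology result and disclosure, or for date error, so there is nothing to reproduce. The check is a comparison of the text, followed by an illustration under stated assumptions.

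**Definition against question**

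| | Definition (Design; Primary outcome) | Question (Primary outcome) | Secured? |
|---|---|---|---|
| Start | First consultation at the hospital | Date she consulted a hospital doctor; 'first' is absent | Mostly: participants are new outpatients approached on reporting |
| End | Diagnosis based on pathology | Date she received the diagnosis; pathology is absent | No |
| Record check | None stated | None stated | Stated only for treatment delay |

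The end date is the substantive half. The start-date wording is minor. It matters at all only because the delay tool appears in the Procedure section at the post-intervention and 3-month assessments, by which time a woman may have had several visits.

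**Women without pathology.** The Abstract says only about 30% of patients who attend with breast abnormalities go on to biopsy. If that background rate applied to all 106 participants, 106 × 0.30 = 31.8, so about 32 would have a biopsy and about 74 would not. This is no forecast for the trial. It shows only that women with no pathology date are not a rare exception.

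**Effect on the comparison.** Let D be the defined delay and g the date answered to the second question minus the pathology date. With a correct start date, measured delay = D + g. Then:

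arm difference in mean measured delay = arm difference in mean D + arm difference in mean g.

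A gap with the same mean in both arms cancels. Each day by which the mean gap differs moves the estimated effect by one day. The documents do not say whether it differs, or in which direction.

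**Random error (illustration only).** Assume a true delay SD of 30 days and an independent date error with SD e. Neither is in the documents. Variance inflation = 1 + e²/30², and effective n per group = 41 / inflation, where 41 is the minimum per group in the Participants section.

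| e (days) | Inflation | Effective n per group |
|---|---|---|
| 7 | 1 + 49/900 = 1.054 | 38.9 |
| 14 | 1 + 196/900 = 1.218 | 33.7 |
| 21 | 1 + 441/900 = 1.490 | 27.5 |

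The same effect can be put as power. With 41 per group, 80% power and two-sided alpha 0.05, the implied standardised difference is √(2/41) × (1.960 + 0.842) ≈ 0.62 by the normal approximation, ignoring clustering. If date error lowered the reliability of the outcome to 0.9, 0.8, 0.7 or 0.5 (assumed values), power would fall from 0.80 to about 0.76, 0.71, 0.65 or 0.51.

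These figures describe noise only. They do not describe an arm-dependent gap, which a larger sample could not repair.

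**The case against.** **Condensed article, tool not final.** The full guide is not shown, it will be piloted, and trained assistants administer it after a 5-day workshop, so prompts may steer the answer to the pathology date. This lowers the likely size of the problem. It does not remove it: the article states which instrument measures the primary outcome and what it asks, and piloting commits the trial to neither a pathology date nor a record source.

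**Disclosure may be the relevant date.** The Abstract speaks of patient diagnosis delay, and the guide separates patient from doctor delay. Redefining the end point as the date she was told would also remove the mismatch. That is true, but the Background, the aim, the Design section and the Primary outcome section all tie the end point to pathology.

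Three stronger readings are tempting and go beyond the documents:

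- *A different interval is certainly measured.* A reader might infer this from the wording. If a woman is told a pathology-based diagnosis on the day it is made, the two intervals coincide. The text shows only that the question does not guarantee this.
- *The result is biased towards PERANTARA.* The package encourages women to seek information from the oncologist, which might bring disclosure forward. It also aims to make them willing to follow the examination procedure, which acts on the defined outcome itself. Nothing shows that disclosure would move without the work-up, and the gap can have either sign.
- *The start date is equally unreliable.* For new outpatients recruited on reporting at the hospital, the consultation asked about will usually be the first. That the answers rest on memory is also an inference from the interview format; the article does not say so.

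**Conclusion.** The point holds in limited form. The stated measurement does not secure the end date of the primary outcome, and no record check closes the gap, although the plan applies one to treatment delay. A different interval can be measured; whether it will be, by how much, and whether unequally between arms cannot be determined from the documents. The missing 'first' is a minor matter of wording.

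The loss from 41 to about 39, 34 or 28 effective women per group rests wholly on the assumed SDs and should not be cited as an estimate. The case for change rests on the validity of the primary outcome and on the low cost of the remedy.

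**What to change.** 1. Take the end date from the pathology report, and verify the first-consultation date in the hospital record. Use the medical-record review already planned for treatment delay and for cancer type, stage and treatment.
2. Reword the first question to ask when she *first consulted at this hospital*, and the second to ask for the date of the pathology-based diagnosis.
3. Record the date she was told as a separate item. It can then be described by arm without standing in for the outcome.
4. Use an interview date only where the record cannot be obtained, and flag it. For the end date, this means only women known to have had a pathological examination whose report is unavailable.
5. Record women without a pathological examination as not yet diagnosed, and do not give them an end date from the interview. A rule demanding two recorded dates for every participant would not work for them.

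The cost is a sentence or two in the outcome definition, two reworded questions, one extra interview item and two extra fields in the record review. Some reports held at other institutions will have to be requested. Because the tool still awaits piloting, the rewording fits into a step already planned.
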